#### Inclusion criteria

Healthy pregnant women aged > 18 yearsSingleton pregnancy (either nulliparous or multiparous)Able to be randomized to group allocation by 17 weeks and six days of gestationPre-pregnancy BMI < 40 kg/m^2^Planning to deliver at a Hamilton, Burlington, or London regional hospital or by home birth and willing to attend research visits at either study siteApproval of primary care provider to participate in exerciseAble to provide signed informed consent

#### Exclusion criteria

Not conversant in EnglishKnown contraindications to exercise as recommended by the Canadian clinical practice guidelines for pregnancy [35]Severe chronic gastrointestinal, heart, kidney, liver, or pancreatic diseases or conditionsRefusal to consume dairy foods due to intolerance or dislikePre-existing diabetesCurrently smoking and will not discontinue smoking during the pregnancyDepression score > 12 on the validated Edinburgh Depression scale

### Randomization: allocation and implementation

Block randomization is used with block sizes of two, four, and six selected at random, using an online Research Electronic Data Capture (REDCap) randomization service managed by an independent team in the Biostatistics Unit at St Joseph’s Healthcare in Hamilton, ON, Canada. Randomization to the two study arms occurs in a 1:1 ratio and is stratified by study site and pre-pregnancy BMI category following IOM guidelines (underweight: BMI < 18.5, normal weight: BMI 18.5–24.9, overweight: BMI 25.0–29.9, and obese: BMI ≥ 30.0 kg/m^2^). The eligibility of participants is confirmed at the first visit, when baseline data are also collected. The research assistant randomizes the participant at the second visit to the study center using an online third-party automatic randomization system. Once randomized, the research assistant consents the participant to the appropriate study arm at a time that is 14–17 weeks/6 days of gestation. Assessments, regardless of the study arm, occur at < 18 weeks of gestation, 26–28 weeks of gestation, 36–38 weeks of gestation, birth, three months postpartum, and six months postpartum. The intervention arm consists of weekly or biweekly in-person visits (based on the participant’s preferences) during pregnancy (i.e. from allocation to study group until 36–38 weeks of gestation). Baseline measures (i.e. before randomization), primary and secondary outcome measures, and other measures assessed during and after pregnancy are measured in all participants, regardless of their study group allocation.

The flow diagram (Fig. 2) will be included in future published results.

**Fig. 1 Fig1:**
[figure not shown]
Flow diagram

This study is open-label due to the nature of the intervention. The study research assistants (data collectors) administering the personalized Nutrition + Exercise intervention are not blinded to group allocation. In addition, the participants are not blinded to their own group allocation, in order to maximize adherence to the lifestyle treatment. Mothers randomized to the intervention and control groups are assessed at the study clinic on different days, to prevent interaction between participants of each study arm. The primary data outcome collector is blinded to group allocation and is conducting the study visits for all participants, regardless of their group allocation. To maximize the objectivity of findings, the primary outcome assessor and data analysts/statistician are blinded to the study allocation and are not collecting any study data.

### Interventions

All participants receive usual care as delivered by their healthcare practitioner (family physician or midwife) during pregnancy. In addition, after enrolment in the RCT and regardless of their group allocation, all participants receive counseling by the study nutritionist on the latest recommendations by Health Canada as published online (https://www.canada.ca/en/health-canada/services/healthy-living/healthy-pregnancy.html). After delivery, both study groups receive usual care from their healthcare practitioners with no further intervention; the research team prospectively follows participants at three months and six months postpartum. Table 1 outlines the study arms.

**Table 1 Tab1:** BHIP study arms

Component	Control arm *Usual care* 12–17 to 36–38 weeks of gestation	Intervention arm *Nutrition + Exercise intervention* 12–17 to 36–38 weeks of gestation
Gestational weight gain (GWG)	Latest recommendation by Health Canada in terms of GWG [17] and the Pregnancy Weight Gain Calculator [44]	Latest recommendation by Health Canada in terms of GWG [17]
Nutrition during pregnancy	Latest recommendation by Health Canada in terms of nutrition during pregnancy [74] and Eating Well with Canada’s Food Guide [46]	Latest recommendation by Health Canada in terms of nutrition during pregnancy [74] **Nutrition component of the intervention**
		1. Individualized nutrition plan with a high protein content: ~ 25% of energy intake which is within the acceptable macronutrient distribution range a. Individualized to each mother’s estimated energy requirement and calculated using the equation derived in the Dietary Reference Intake report for women [43] with energy intakes adjusted as recommended in the second and third trimesters [74] b. Provided by dairy foods: 4–5 servings of dairy food/d: fresh low-fat white milk and/or cottage cheese and/or low-fat Greek yogurt, as implemented in our previous study [38]
Exercise during pregnancy	Latest recommendation by Health Canada in terms of exercise during pregnancy [75]	Latest recommendation by Health Canada in terms of exercise during pregnancy [75] **Exercise component of the intervention**
		1. Controlled walking program with the study nutritionist a. 25 min per session, 3–4 times per week, while increasing the time by 2 min/week to a maximum of 40 min maintained until delivery [39] 2. 10,000 steps per day a. Daily step counts and any other exercise tracked using a pedometer every day and an exercise log. Also used as a motivator and self-monitoring device which will also help improve compliance [39]
Wellbeing during pregnancy	**Nested qualitative study**	
	1. Focus group and information session given by a midwife in the third trimester of pregnancy a. Discussion on topics such as pain relief options during labor and breastfeeding techniques	

Participants randomized to the personalized, monitored, and structured Nutrition + Exercise program group (intervention) begin early in the second trimester of their pregnancy until the end of pregnancy with counseling on a weekly or biweekly basis (Table 1 and Fig. 1). The nutrition component is an individualized nutrition plan tailored to each participant’s energy requirements with a high protein content (25% protein energy) provided primarily by dairy foods. Dairy foods are accepted by women during pregnancy as a healthy choice as indicated from our pilot study [36] and in a recent birth cohort study in the same community in which women consumed an average of ≥ 3 servings of dairy foods per day [37]. Dairy foods are sources of high-quality proteins, calcium, and vitamin D in the case of milk as it is under mandatory fortification with vitamin D in Canada. The Nutrition + Exercise intervention is considered safe. First, the nutrient intake associated with the increased low-fat dairy consumption is less than the tolerable upper intake level for all nutrients as recommended per the Dietary Reference Intake by Health Canada. In addition, walking (the exercise component) is the easiest physical activity to undertake and implement in terms of goal-setting for step count and monitoring adherence using accelerometer-type devices as demonstrated in our previous studies [38–40]. Walking was the most practical exercise intervention of choice since women reduce moderate and vigorous physical activity during pregnancy yet maintain levels of walking [41]. Most importantly, these exercise guidelines are based on the Physical Activity Readiness Medical Examination (PARmed-X) for Pregnancy [35]. Data from the Nutrition and Exercise Lifestyle Intervention Program study [39] indicates that the goal of 10,000 daily steps is feasible under free-living conditions and has been effectively utilized in a number of trials [42].

**Fig. 2 Fig2:**
[figure not shown]
BHIP study protocol timeline

A component of the intervention is discontinued if the medical condition of a participant changes and the intervention is modified if a participant requests a change due to personal reasons, such as food aversion or pain episode. The intervention is personalized for every woman, to ensure the goal of 25% energy from protein and 10,000 steps/day are achieved. Additionally, estimated energy requirements are calculated for each mother using the equation derived in the Dietary Reference Intake report for normal and overweight women [43] with energy intakes adjusted as recommended in the second and third trimesters [17]. The individualized nutrition plan is fashioned upon a standard three-day food intake record completed by the mothers that includes one weekend day as used previously in pregnant women [39]. The individualized nutrition plans and counseling are conducted by a study nutritionist providing the number of food servings to meet their estimated energy requirements. The nutrition plan is modified if GWG monitoring indicates weight loss or excess gain has occurred as recommended in the GWG guidelines [17, 44]. Adverse events related to the intervention are reported to our local ethics boards. Other non-intervention-related adverse events are noted in the participant’s chart and monitored, in accordance with the N2 Network of Networks guidelines Canada [45].

Several strategies are used to improve adherence to the intervention. For the exercise component, participants wear and track their step counts on a weekly basis, increasing motivation and adherence to the treatment. In addition, they go for a walk with the research staff and have a personalized counseling session with the study nutritionist. For the nutrition component, participants are provided with low-fat milk, cottage cheese, and/or yogurt, as per their preference, to ensure they consume the recommended amount of dairy foods. Participants come to the study site at least every other week to receive their dairy foods and the study nutritionist shares strategies and recipes with the participants to ensure they consume the targeted amount of dairy food servings. All these actions improved the adherence to the study protocol.

Participants randomized to the usual care group (control) receive usual prenatal care. Participants are given the most recent advice from Health Canada including Healthy Weight Gain During Pregnancy [17], the Pregnancy Weight Gain Calculator [44], and Eating Well with Canada’s Food Guide [46]. Mothers are followed by their primary care provider who also receives the same Health Canada materials. After delivery, they are followed by their healthcare practitioners. In addition, the control participants are invited to participate in a focus group and to attend an information session led by a midwife; topics discussed include pain relief options during labor and breastfeeding techniques (Table 1).

## Outcome measurements

Primary and secondary outcomes are summarized in Table 2 and described below.Primary outcome○ GWGSecondary outcomes○ Maternal and cord blood circulating bone markers: PINP, CTX-I, IGF-1, 25(OH)D, 1,25dihydroxyvitamin D○ Maternal bone status at six months postpartum: whole-body bone mineral content (BMC), whole body BMD, lumbar spine BMD○ Infant bone status at six months of age: whole body minus the head BMCOther outcomes○ Maternal body weight and fat mass○ Maternal metabolic status (including fasting glucose and lipid profiles, leptin and adiponectin)○ Maternal blood pressure○ Maternal pregnancy outcomes such as gestational diabetes and pre-eclampsia○ Infant birth outcomes such as birth weight and body fat mass at six months○ Safety outcomes○ Quality of life using the EQ-5D questionnaire○ Healthcare costs○ Maternal and cord blood gene variant profiles

**Table 2 Tab2:** Analysis plan: objectives, outcomes, hypotheses, and methods of analysis

Objective	Hypothesis	Outcome measure (type of outcome: B = binary or C = continuous)	Methods of analysis
1. Primary	An experimental combined Nutrition + Exercise intervention will increase the percentage of pregnant women who achieve GWG within current recommendations when compared with standard care provided in the primary care community setting	Proportion of women who are within the BMI appropriate GWG according to the IOM guideline for GWGs (B)	Logistic regression
2. Secondary	An experimental combined Nutrition + Exercise intervention will lead to better maternal and child bone health outcomes when compared to standard care	*• Maternal and cord blood circulating bone markers (C)* ○ Bone biomarkers: PINP, CTX-I, IGF-1, 25(OH)D, 1,25(OH)_2_D *• Maternal bone status at 6 months postpartum (C)* ○ Whole body bone mineral content, whole body BMD, lumbar spine bone mineral density by DXA scan *• Maternal fat mass (C)* *• Maternal blood glucose, lipid profile, leptin, and adiponectin* *• Maternal blood pressure (C)* ○ Diastolic BP ○ Systolic BP *• Maternal pregnancy outcomes (B)* ○ Gestational diabetes ○ Pre-eclampsia *• Infant bone status at 6 months of age (C)* ○ Whole body minus the head bone mineral content by DXA scan *• Infant outcomes* ○ Birth weight z-score(C) ○ Body fat mass (B)	Regression analysis *We will use logistic regression for binary outcomes and linear regression for continuous outcomes
3. Subgroup analyses	The percentage of women within each of the normal, overweight, and obese BMI categories will be similar with respect to being with the IOM target GWG for each category	Proportion of women in each BMI category who reach appropriate GWG according to the IOM guideline for GWGs	Regression analysis including the interaction term of BMI group X Intervention group
4. Sensitivity analyses	Combined Nutrition + Exercise Intervention leads to a greater percentage of women who achieve GWG within current recommendations when compared to standard care	Primary outcome only	***•*** Generalized estimating equations ***•*** Random-effects model

IMPORTANT REMARKS:

In all analyses, results will be expressed as difference or OR (95% CI) and associated *p* values, as appropriate

Bonferroni method will be used to adjust the overall level of significance for multiple secondary outcomes

We will examine residuals to assess model assumptions

The GEE [76] is a technique that allows to specify the correlation structure between patients within a site and this approach produces unbiased estimates under the assumption that missing observations will be missing at random. An amended approach of weighted GEE will be employed if missingness is found not to be at random [77]

*Infant growth outcomes at 6 months will be adjusted for feeding type (duration of breast feeding from birth to 6 months)

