### Specific objectives and hypothesis

The primary research objective of the Be Healthy in Pregnancy (BHIP) study is to determine whether introducing a structured and monitored nutrition (high-dairy protein diet) and exercise (walking) program (intervention) in early pregnancy, compared to standard prenatal care (control), will increase the number of women attaining GWG (outcome) within the Institute of Medicine (IOM) recommendations for their pre-pregnancy body mass index (BMI) sub-category [17].

Secondary objectives include determination of the impact of a maternal high-dairy diet with exercise compared to standard care diet during pregnancy on: (1) bone status (e.g. blood biomarkers procollagen type I that contains N-terminal extensions (PINP), C-terminal telopeptide of type I collagen (CTX-I), insulin-like growth factor-1 (IGF-1), 25-hydroxyvitamin D (25(OH)D), and 1,25-dihydroxyvitamin D) in mothers during pregnancy; (2) infant bone status at birth via cord blood; and (3) mother and infant bone status at six months postpartum by dual energy x-ray absorptiometry (DXA) scan.

The over-arching hypothesis is that maternal consumption of a high-dairy diet during pregnancy will have a positive impact on: (1) GWG; (2) bone health status of the mother during and after pregnancy; and (3) bone mass and bone size of the offspring, after adjustment for factors known to influence skeletal status.

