### Data and biosample collection

The pre-pregnancy BMI is calculated using the measured weight at study entry minus the mother’s self-reported GWG. Body weight is measured by trained research assistants using a body impedance Tanita Body Composition Analyzer BF-350 scale (Tanita, IL, USA) at 12–17 weeks of gestation, 26–28 weeks of gestation, 36–38 weeks of gestation, three months postpartum (self-reported weight only), and six months postpartum. GWG is calculated by subtracting the weight at the 36–38 weeks of gestation study visit by the pre-pregnancy weight. Adjustments such as rate of GWG will be made to account for gestational age at delivery, including pre-term births.

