At six months postpartum, bone scans are performed on mothers and infants at six months by staff following a standard operating procedure. Mothers are dressed in regular clothes without any metal parts or in a light hospital gown, while infants are in a clean diaper only. The primary outcome assessor, who has expertise in analyzing DXA scans, reviews all scans from both study sites. This ensures consistency in analysis across all participants at both study sites. If objects are included in the scan such as a child’s toy, a sub-regional analysis is done to isolate and subtract the object’s contribution to overall results. If considerable movement artifacts are seen in infant scans, the well-captured limb is used as a surrogate for the one with movement [50]. Any scans with unsalvageable distortions due to movement are not included. Z-scores are calculated for all BMC and BMD results using data from an age- and sex-specific standard curve. Results for women are interpreted as z-scores in reference to an adult women population embedded in the Hologic software. Results for infants are expressed as whole body minus the head BMC and BMD. Data are interpreted as z-scores in reference to an infant population from in-house data collection on normal healthy term infants from birth to one year of age.

All participants receive instructions to complete a standard three-day food intake record at 12–17 weeks of gestation, 26–28 weeks of gestation, 36–38 weeks of gestation, and six months postpartum. The food record includes two weekdays and one weekend day, as used previously in pregnant women [39]. It captures food and beverage intake as well as drug and supplement (vitamin and mineral) intake. Trained assessors analyze all food records using standard operating procedure on the computer-based Nutritionist Pro Software (Axxya Systems, Stafford, TX, USA). Nutritionist Pro computes the average amount of nutrients consumed per day.

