### Statistical methods

The analysis and reporting of the results will follow the SPIRIT statement for reporting RCTs [53]. The process of patient selection and flow throughout the study will be summarized using a flow-diagram (Fig. 2).

The results of patient baseline characteristics and outcome variables (both primary and secondary) will be summarized using descriptive summary measures: expressed as mean (standard deviation) or median (range) for continuous variables and n (%) for categorical variables. All statistical tests will be performed using two-sided tests at the 0.05 level of significance. Binary outcomes will be analyzed using logistic regression and continuous outcomes will be analyzed using linear regression. All analyses will account for stratification by including study site and participants’ BMI category in the models. For all models, the results will be expressed as estimate of the difference for continuous outcomes (odds ratio [OR] or relative risk [RR] for binary outcomes), corresponding two-sided 95% confidence intervals (CI) and associated *p* values. *P* values will be reported to three decimal places with values < 0.001 reported as < 0.001. The Hosmer–Lemshow will be used to assess goodness-of-fit for logistic regression and explore the residuals to assess goodness-of-fit and model assumptions for linear regression.

An intention-to-treat principle will be adopted to analyze all outcomes. Multiple-imputation will also be used to handle missing data during data collection. Sensitivity analyses will be performed using some of the commonly used RCT patient-level methods (e.g. generalized estimating equations, the random-effect model which account for the potential correlation within sites, etc.) to assess the robustness of the results [54]. All the analyses will be done using SAS 9.2 (Cary, NC, USA) or SPSS 13 (Chicago, IL, USA). Table 2 provides a summary of the planned methods of analyses for each outcome and subgroup.

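### Maternal six-month bone outcomes have no baseline scan, and the analysis text names only site and BMI category for them; naming the woman's height as a covariate would recover precision, mainly for whole-body BMC

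*Protocol article*

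**What the plan says.** **Outcomes.** Table 2 (Outcome measurements) lists the maternal DXA outcomes under the secondary objective as continuous measures at six months postpartum: "Whole body bone mineral content, whole body BMD, lumbar spine bone mineral density by DXA scan".

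**Timing.** Data and biosample collection gives one scanning occasion: "At six months postpartum, bone scans are performed on mothers and infants at six months by staff following a standard operating procedure". No scan before randomisation is described.

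**Model.** Statistical methods says "continuous outcomes will be analyzed using linear regression". On covariates it says: "All analyses will account for stratification by including study site and participants’ BMI category in the models".

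**Further adjustment.** Two places go beyond site and BMI category. A note to Table 2 says "Infant growth outcomes at 6 months will be adjusted for feeding type (duration of breast feeding from birth to 6 months"), which does not concern the mother's own scan. The over-arching hypothesis (Specific objectives and hypothesis) lists weight gain, maternal bone and offspring bone, and its last item reads "bone mass and bone size of the offspring, after adjustment for factors known to influence skeletal status". The factors are not listed there or elsewhere in the article.

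**Standardisation.** DXA results are also turned into z-scores from curves specific to age and sex. Height is not mentioned.

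**The concern.** With no baseline scan, the most useful covariate for a bone outcome is unavailable. What remains is whatever pre-randomisation information on body size the model uses. BMI category is the only such term named, and it is poorly suited to the purpose: BMI divides weight by height squared, so two women in the same category can differ widely in stature. Whole-body BMC is a total mineral mass and is larger in a larger skeleton. Z-scores by age and sex leave that variation in place.

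Randomisation balances height on average, so the estimated difference between arms is not biased. The loss is one of precision: ordinary differences in body size between women stay in the residual variance of a declared secondary outcome. Precision is scarce in this trial. The target was cut from 350 to 242, and a Bonferroni adjustment applies across the secondary outcomes.

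There is also a gap in the wording. The hypothesis announces adjustment for skeletal factors, and the analysis text does not say which factors or for which bone outcomes. That leaves room for covariates to be chosen once data are in hand.

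**Working it through.** **No stated figure to reproduce.** Power calculation gives totals of 177 for maternal bone biomarkers and 240 for infant BMD, but nothing for maternal DXA: no difference, SD or power.

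**Inputs from the article.** 242 women, 1:1, so 121 per arm; 15% attrition, the rate used for the bone calculations; two-sided 0.05; Bonferroni for secondary outcomes, number of tests not stated.

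**Input assumed.** r is the correlation of height with the outcome within site and BMI category. The article does not give it. I use 0.3 to 0.7 for whole-body BMC and 0.2 to 0.3 for BMD.

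**Step 1: effect of height on residual variance.** Residual variance is multiplied by 1 − r², interval width by √(1 − r²), and the equivalent sample size by 1/(1 − r²).

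| r | Fall in residual variance | Narrower interval | Equivalent extra women |
|---|---|---|---|
| 0.2 | 4% | 2% | 4% |
| 0.3 | 9% | 5% | 10% |
| 0.5 | 25% | 13% | 33% |
| 0.7 | 49% | 29% | 96% |

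**Step 2: detectable difference.** Women with a scan per arm: 121 × 0.85 = 102.85. At 80% power and two-sided 0.05, before any multiplicity adjustment, the detectable difference without height is (1.960 + 0.842) × √(2/102.85) = 0.39 SD. Multiplying by √(1 − r²) gives 0.37 SD (r = 0.3), 0.34 SD (r = 0.5) and 0.28 SD (r = 0.7).

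**Step 3: power at 0.39 SD, as illustration only.** Power = Φ(0.39/√(1 − r²) × √(102.85/2) − z). Without height the first term is 0.39 × 7.171 = 2.797.

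| Significance level | No height | r = 0.3 | r = 0.5 | r = 0.7 |
|---|---|---|---|---|
| 0.05 (z = 1.960) | 80% | 83% | 90% | 97.5% |
| 0.05/3 (z = 2.394) | 66% | 70% | 80% | 94% |
| 0.05/14 (z = 2.914) | 45% | 51% | 62% | 84% |

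The divisor 3 counts the maternal DXA outcomes alone. The divisor 14 counts the outcome list at its shortest: five markers in maternal and in cord blood (10), three maternal DXA outcomes and one infant outcome. The article fixes neither count. Height helps in every row, but the absolute power depends on a divisor and an effect size that the article does not give.

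**Step 4: cost of the extra term.** About 206 women would have scans. The model with intercept, arm, site (one term) and BMI category (three terms) has six parameters, leaving about 200 residual degrees of freedom. Height takes one of these, about 0.5%, which is small against a 9% fall in variance at the low end for BMC.

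**Step 5: is height available?** Inclusion criteria set an upper limit on pre-pregnancy BMI, and randomisation is stratified by BMI category, so a height must exist for every woman before allocation. The article describes only the weight side: "The pre-pregnancy BMI is calculated using the measured weight at study entry", less the reported gain. It does not say whether height is measured or self-reported.

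**The case against.** The strongest objection is that the article does not exclude height. A reader might infer that the models hold site and BMI category and nothing else. Statistical methods does not say that: it says the stratification factors will be included, which sets a minimum. The feeding-type note shows that terms are added for particular outcomes, and the hypothesis speaks of adjusting for skeletal factors, among which body size would be an obvious candidate. A fuller covariate list may also sit in an analysis plan that is not shown. This part of the objection stands, so the point cannot be that the plan rules height out.

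It does not dispose of the matter. Table 2 is presented as the analysis plan, and it names a covariate where one was thought necessary. For maternal DXA it names none. The phrase in the hypothesis can be read as attached to offspring bone alone, lists no factor, and is not taken up in the analysis text. As published, the places do not fit together for these outcomes.

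Three further objections are fair and limit the claim. The correlation is assumed, and across the range used the gain runs from small to large. Power figures at 0.05 overstate what the trial would have after Bonferroni. The benefit is material for one of the three outcomes and small for the two BMD measures. Finally, leaving out a prognostic covariate is valid, so this concerns efficiency and clarity.

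**Conclusion.** The point holds as one of efficiency and unfinished specification on a secondary outcome. Maternal bone is scanned once, after the intervention. The covariates named in the analysis text carry little information on height, and the adjustment announced in the hypothesis is not defined for these outcomes. If height is left out, residual variance of maternal whole-body BMC is larger than it need be. Adding height would reduce it by 9–49%, equal to about 10–96% more women (33% at r = 0.5), on an assumed correlation of 0.3 to 0.7. For BMD the gain is about 4–10%, on an assumed 0.2 to 0.3.

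Two stronger readings are not supported. The article does not confine the models to site and BMI category. Nor is the comparison between arms biased, since height is balanced by randomisation on average. The power figures are illustrations: the article gives no effect size or SD for maternal DXA and does not fix the Bonferroni divisor. The absence of a baseline scan is a feature of the design. It makes height more useful, but is not itself an error.

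**What to change.** In Statistical methods and in the maternal bone row of Table 2, carry the wording of the hypothesis through. State that the maternal six-month DXA outcomes, above all whole-body BMC, are analysed by linear regression with terms for arm, site, BMI category and the woman's height, entered as a continuous variable and taken as recorded for her pre-pregnancy BMI. Say whether that height is measured or reported. Keep the model without height as a supportive analysis. Do not use six-month weight as the body-size term: it is measured after randomisation and the intervention could affect it.

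In Specific objectives and hypothesis, say whether the adjustment covers maternal bone as well as offspring bone, and point to the named covariates.

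The cost is a sentence or two of wording and one model term. No new data collection is needed, provided the recorded height is kept in the trial database. The change should be dated before the maternal DXA data are analysed by arm.

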**Methods:**

The BHIP study is a two-site RCT that will recruit up to 242 participants aged > 18 years at 12–17 weeks of gestation. After baseline measures, participants are randomized to either a structured and monitored Nutrition + Exercise (intervention) or usual care (control) program for the duration of their pregnancy. The primary outcome of the study is the percent of women who achieve GWG within the Institute of Medicine (IOM) guidelines. The secondary outcomes include: (1) maternal bone status via blood bone biomarkers during pregnancy; (2) infant bone status in cord blood; (3) mother and infant bone status measured by dual-energy absorptiometry scanning (DXA scan) at six months postpartum; (4) other measures including maternal blood pressure, blood glucose and lipid profiles, % body fat, and postpartum weight retention; and (5) infant weight z-scores and fat mass at six months of age.

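### Table 2 codes infant body fat mass as binary, which under the plan's own rule sends a continuous quantity to logistic regression; probably a slip, but wrong as written

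*Protocol article*

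**What the plan says.** Table 2 of the Protocol article (Outcome measurements) is headed as the analysis plan. Its outcome column defines the codes: "type of outcome: B = binary or C = continuous". In the row for the secondary objective, under infant outcomes, the entry is "Body fat mass (B". The methods column of that row states: "We will use logistic regression for binary outcomes and linear regression for continuous outcomes". The Statistical methods section repeats the rule: "Binary outcomes will be analyzed using logistic regression and continuous outcomes will be analyzed using linear regression". It also refers to Table 2 for the planned method for each outcome.

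Three other places bear on the entry:

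- The same Table 2 row codes the mother's variable the other way: "Maternal fat mass (C".
- The abstract lists "infant weight z-scores and fat mass at six months of age".
- The outcome list ahead of Table 2 gives "Infant birth outcomes such as birth weight and body fat mass at six months", under other outcomes.

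None of these mentions a category or a threshold.

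**The concern.** The outcome code decides the model. A B entry calls for logistic regression, which needs a yes/no variable, and the article defines none for infant fat mass. An analyst following the table would have to split a measured quantity. The reported effect would then be an odds (or risk) ratio across the cut instead of a difference in fat mass, with less precision than the data allow.

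The objection is to what the table states, not to missing detail. The other B entries in Table 2 (weight gain within the guideline, gestational diabetes, pre-eclampsia) are true yes/no outcomes. Infant fat mass is the only measured quantity coded B. Offspring obesity is part of the trial's rationale, so this outcome will be read with interest even though it is not primary.

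**Working it through.** **1. What the text implies.** Code B means binary, and binary means logistic regression (Table 2 and Statistical methods). Infant fat mass is coded B, so it goes to logistic regression. Maternal fat mass is the same kind of variable, is coded C, and goes to linear regression. The two entries conflict, and nothing in the article explains the difference.

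**2. No figure to reproduce.** The Power calculation section gives no sample size, effect or SD for infant fat mass. Everything below is what would follow if the B code were obeyed.

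**3. Information lost by splitting.** Assume a normal outcome whose mean shifts between arms. With a share p above cut c, the efficiency of the split relative to a comparison of means is φ(c)² / [p(1−p)].

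| Share above cut | φ(c) | Relative efficiency | Loss | Sample size factor |
|---|---|---|---|---|
| 50% | 0.399 | 0.1592/0.25 = 0.637 | 36.3% | 1.57 |
| 25% | 0.318 | 0.1010/0.1875 = 0.539 | 46.1% | 1.86 |
| 10% | 0.175 | 0.0308/0.09 = 0.342 | 65.8% | 2.92 |

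The median split, at 2/π, is the best case. The shares above the cut are assumptions, because the article gives none.

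**4. Illustrative power.** Inputs:

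- Number of infants: 240 is the total in the Power calculation section for infant whole body minus head BMD, a different outcome. Less the 15% attrition stated there, 240 × 0.85 = 204, or 102 per arm.
- Alpha: 0.05 two-sided (Statistical methods), without the Bonferroni adjustment that Table 2 plans for secondary outcomes.
- Effect: solved for 80% power as continuous, d = (1.960 + 0.842) × √(2/102) = 0.392 SD.

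With p₁ the control share above the cut, p₂ = 1 − Φ(c ∓ d), p̄ the mean of p₁ and p₂, and n = 102 per arm, power for two proportions is Φ{[|p₁−p₂| − 1.96√(2p̄(1−p̄)/n)] / √([p₁(1−p₁)+p₂(1−p₂)]/n)}.

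Median split, written out: p₁ = 0.500, p₂ = 0.347, difference 0.1526. The null term is 1.96 × 0.0692 = 0.1356 and the alternative SE is 0.0684. Then (0.1526 − 0.1356)/0.0684 = 0.248, and Φ(0.248) = 0.598.

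| Control share above cut | p₂ if fat mass falls | Power | p₂ if fat mass rises | Power |
|---|---|---|---|---|
| 50% | 0.347 | 60% | 0.653 | 60% |
| 25% | 0.143 | 49% | 0.389 | 57% |
| 10% | 0.047 | 30% | 0.187 | 42% |

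Backing the effect out of the t distribution gives d = 0.394 instead of 0.392 and moves the last figure to 43%. The efficiencies in step 3 are local approximations that ignore direction. Applied directly they give about 61%, 54% and 37%, inside or within a point of these ranges.

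**The case against.** The strongest reply is that B is simply a slip for C. The abstract and the outcome list name a quantity, the maternal variable is C, and nothing else in the article points to a split infant outcome. Table 2 is also uneven elsewhere: the line for maternal glucose, lipids, leptin and adiponectin carries no code at all. This stands as the likelier reading. On it, no information would be lost, and only the letter needs correcting.

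A reader might infer three stronger things, none of which the article supports:

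- **That the trial will discard a third or more of its information on this outcome.** That follows only if the code is obeyed, and the text suggests it may not be meant.
- **That a threshold would be picked from the data.** The article is a condensed account, and a fuller plan may define a cut-point or correct the code. A binary version could also use an external reference cut. The missing threshold shows only that the article does not explain the B.
- **That a DXA measurement is being split.** The section on data collection says "bone scans are performed on mothers and infants at six months by staff" and describes DXA for bone. It gives no method for infant fat mass, so DXA is an inference. The point does not need it, since fat mass is continuous however it is measured.

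The power figures are also open to challenge: they borrow the infant BMD sample size, a back-solved effect and assumed cuts, and they ignore Bonferroni. They show scale only. The efficiency figures depend on none of these except the cuts and the normal shift model.

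Last, the impact is modest. The outcome list places this variable among other outcomes, while the abstract and Table 2 treat it as secondary. It does not drive the sample size.

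**Conclusion.** The point holds in limited form. Table 2 as printed assigns the wrong outcome type, and through it the wrong model, to infant body fat mass. It conflicts with the nature of the variable and with the maternal entry in the same row. That is an error in a stated analysis rule, most likely clerical.

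Its size is conditional on the code being followed: a loss of at least about 36% of the information under a normal shift model, and more for any cut away from the median. On the illustrative inputs, 80% power becomes about 60% at a median split, 49–57% at a quartile cut and 30–43% at a 10% cut. It should be corrected, but it does not touch the primary result.

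**What to change.** In Table 2, change the code for infant body fat mass from B to C. Analyse it by linear regression with study site and BMI category in the model, as the Statistical methods section requires. Keep the Table 2 footnote's adjustment of six-month infant growth outcomes for feeding type where it applies, and say whether fat mass counts as one of them. Report a mean difference with a 95% CI.

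If a binary outcome really was intended, state the threshold and its source before unblinding.

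The cost is one letter and a short clarification in the analysis table. No participant, procedure or data item changes.
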